## **Vital signs**

Vital signs variables include measurements of oral body temperature, systolic and diastolic blood pressures, pulse and body weight. Vital signs will be examined for abnormal values and change from Baseline according to pre-specified clinically notable criteria (see [Appendix 2](#)). Appropriate incidence rates of clinically notable abnormalities for between-group differences will be provided. Shifts from baseline value to worst post-baseline value based on the normal ranges/notable criteria will be presented graphically ([Amit et al., 2008](#)). The worst observation is defined as the highest or lowest measure during the different observations periods whereby high or low are chosen according to the direction of abnormality. Further, descriptive

statistics of change from baseline of all vital signs variables will be presented by visit. A by-patient listing of all clinically notable abnormal vital signs will be generated. Only assessments obtained up to 7 days after the discontinuation of study medication will be considered “on-treatment”.

### **Cardiovascular risk (Framingham Score)**

At BL1, BL2, Month 6, and at follow-up visits the cardiovascular risk will be calculated using the Framingham Score (see [Appendix 7](#)). Descriptive statistics for changes from BL1 to BL2 and from BL2 to Month 6 will be presented. Changes from baseline will be tested using adequate tests.

### **10.5.3 Tolerability**

Tolerability of study medication will be assessed from the rate of patients who withdraw prematurely from study medication or in whom study medication had to be converted to another immunosuppressive regimen due to abnormal laboratory results or adverse events. A number of reasons are pre-defined in [Section 7.7](#) of this protocol. The frequency distribution of these reasons will be presented with absolute and percent values. The most frequent reasons (total  $n \geq 5$ ) for discontinuation and/or conversion as well as the total number of patients who are affected by such intolerability of study medication will be compared between the treatment groups using Fisher’s exact test.

### **10.5.4 Resource utilization**

Not applicable.

### **10.5.5 Health-related Quality of Life**

Not applicable.

### **10.5.6 Pharmacokinetics**

Analysis of the cyclosporine blood levels and Certican® (everolimus) blood levels will be done by treatment group for the treatment phase (up to Month 6) and separately during the follow-up phase.

Blood level values of cyclosporine will be summarized by descriptive statistics by visit and treatment group. The number of patients with deviations from the therapeutic window (see [Section 6.5.2](#)) will be counted and tabulated by visit and in total.

Trough levels of everolimus will be summarized descriptively by visit up to Month 6. The number of patients with deviations from the therapeutic window (see [Section 6.5.1](#)) will be counted and tabulated separately by visit and in total.

### **10.5.7 Pharmacogenetics/pharmacogenomics**

Not applicable.

### **10.5.8 Biomarkers**

Biomarker variables (e.g. CD25 saturation) will be analyzed separately and reported in an extension to the Clinical Study Report.

### **10.6. Interim analysis**

No interim analysis is planned.

### **10.7 Sample size calculation**

From data for the subgroup of elderly patients in study CRAD001A2418, the probable difference in the GFR (Cockcroft-Gault) between the CNI-free regimen group and the standard regimen group is estimated as  $\delta = 8$  ml/min with a standard deviation of 16 ml/min at Month 6 after transplantation. Assuming a difference in the mean GFR of 8 ml/min (60 ml/min in the CNI-free group and 52 ml/min in the standard regimen group) and a common standard deviation of 19 ml/min, a two-group t-test with a 5% two-sided significance level will have 80% power to detect this difference when the sample sizes in the CNI-free group is 135 and in the standard regimen group is 68, respectively (a total sample size of 203). Taking into account a common drop-out rate of 10%, 162 patients need to be randomized into the CNI-free group, and 82 into the standard regimen group (a total drop-out adjusted sample size of 244 patients). Enrollment will be continued until the required sample size will be achieved.

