### Population:

The study population consists of a representative group of approx. 240-260 senior de novo kidney transplant patients (patients will be randomized in a 1:2 ratio at Week 7 to either the Control or the Certican group; 82 patients in Control arm, 162 patients in Certican arm). Enrollment will be continued until the required sample size will be achieved. The patients will be recruited from about 8 – 12 transplant centers in Germany.

---

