## 5 Population

The study population will consist of a representative group of approximately 240-260 *de novo* senior kidney transplant patients participating at the Eurotransplant senior program (ESP). These patients will be randomized at Week 7 to either the Control arm or the Certican arm in a 1:2 ratio; 82 patients in the control arm, 164 patients in Certican arm. Enrollment is planned for 24 months, but will be continued until the required sample size will be achieved. The patients will be recruited from about 8 – 12 transplant centers in Germany.

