## **6.3 Treatment assignment**

A randomization list will be produced by or under the responsibility of Novartis Biometrics Department using a validated system that automates the random assignment of treatment groups to randomization numbers in the specified 2:1 ratio (Certican®, Control). Two sets of randomization numbers will be prepared for stratified randomization, one set for the group of patients who did not experience any rejection between Baseline 1 and Baseline 2 (Visit 3/Week 7) and one set for the group of patients who did experience at least one rejection in this period. Randomization numbers will be different in the two sets. The randomization scheme will be reviewed and locked after approval. According to the recommendations given in the ICH E9 Guideline "Statistical Principles for Clinical Trials" (CPMP, 1998), the used block length is specified in a separate document which is withheld from the study centers. The randomization list will be kept sealed in a secure location.

At Baseline 1 which has to be performed prior to the transplantation surgery, patients will be assigned a unique patient identification by the investigator. The patient identification has two parts. The first part is the four-digit center number, which is assigned by Novartis. The second part will be assigned by the investigator starting with number "00001" in each study site. Once assigned to a patient, the patient identification will not be reused. If the patient fails to be randomized for any reason, the patient's identification and the reason for not being randomized will be entered on

the Study Completion Page. Note: The patient identification is different from the randomization number.

At Baseline 2 (visit 3, Week 7), all eligible patients will be given a randomization number that assigns them to one of the treatment groups. The randomization numbers are sequentially allocated to the patients per center in the order of inclusion in the randomized treatment period. Each patient will receive only that treatment regimen which is labeled with the randomization number allocated to him/her.

Randomization of individual patients will be performed centrally by the designated CRO. Allocation of a patient to one of the two treatment groups will be performed in the following steps.

1. Information about patient inclusion (BL 1)  
Study sites will inform the randomization department of the designated CRO about each patient inclusion via fax

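### The randomized total of 244 does not follow from the stated 10% drop-out (it implies about 17%), and Section 5 gives 164 instead of 162 for the Certican arm

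*Protocol*

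**What the plan says.** Protocol Section 10.7, repeated in the synopsis under Sample size, plans for a two-sided 5% t-test. The SD is set at 19 ml/min in both arms, and the expected GFR difference between the arms at 8 ml/min (60 against 52). It concludes that 135 evaluable patients in the CNI-free arm and 68 in the standard arm (203 in total) give 80% power. The next sentence reads: "Taking into account a common drop-out rate of 10%, 162 patients need to be randomized into the CNI-free group". The standard arm is put at 82 and the drop-out-adjusted total at 244.

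The synopsis paragraph on the population agrees: "82 patients in Control arm, 162 patients in Certican arm". Section 5 does not: "82 patients in the control arm, 164 patients in Certican arm", which sums to 246. The synopsis and Sections 4 and 5 also give an approximate range of 240-260 patients. Recruitment is to continue until the required number is reached, and Section 10.6 plans no interim analysis.

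**The concern.** Going from 203 evaluable to 244 randomized patients is a 20% increase, while the reason given is a 10% loss. Rounding cannot produce that gap, and no further allowance is mentioned. A reader therefore cannot tell whether the rate, the formula or the arm sizes are wrong, and the possible readings point in opposite directions. If 10% is the planned loss, the protocol calls for more patients than its own assumptions require. If a higher rate such as 20% was meant, 244 is slightly too few.

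This number is the recruitment target, and the stated rate is what the loss actually observed will be compared with. It also indicates how much of the primary outcome the multiple imputation in Section 10.4.3 is expected to supply. Two different Certican targets in current text add to the ambiguity.

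**Working it through.** **Inputs** (Section 10.7; allocation from Section 6.3): difference 8 ml/min; SD 19 ml/min; two-sided alpha 0.05; power 80%; allocation 2:1 Certican to control; evaluable 135 and 68; drop-out 10%; randomized 162 and 82.

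**Step 1. Reproduce the evaluable numbers.** For a two-sample t-test the noncentrality parameter is δ / (σ·√(1/n₁ + 1/n₂)).

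- 135 and 68: 8 / (19·√(1/135 + 1/68)) = 2.831 on 201 degrees of freedom. Power is 80.5%.
- 134 and 67: power is 79.97%, just short of 80%.

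So 135 + 68 = 203 is correct.

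**Step 2. Apply 10% drop-out.** The randomized number is n / (1 − d).

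| Method | CNI-free | Standard | Total |
|---|---|---|---|
| n / 0.90 | 150 | 75.6 → 76 | 226 |
| n × 1.10 (the usual shortcut) | 148.5 → 149 | 74.8 → 75 | 224 |
| n / 0.90² (10% applied twice) | 166.7 → 167 | 84.0 → 84 | 251 |
| **Protocol** | **162** | **82** | **244** |

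None of these reproduces 162 and 82.

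**Step 3. Find what does reproduce them.** A factor of 1.2 does: 135 × 1.2 = 162.0; 68 × 1.2 = 81.6, rounded up to 82; 203 × 1.2 = 243.6, rounded up to 244. The implied loss is

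- CNI-free: 1 − 135/162 = 16.7%
- Standard: 1 − 68/82 = 17.1%
- Overall: 1 − 203/244 = 16.8%

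A factor of 1.2 would also arise if 20% drop-out were multiplied on instead of divided out. A correct 20% inflation is 135/0.8 = 168.75, rounded up to 169, and 68/0.8 = 85, a total of 254. So 244 matches neither 10% nor a correctly applied 20%.

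**Step 4. Power with 162 + 82 randomized** (same t-test, completers only):

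| Actual loss | Evaluable | Power |
|---|---|---|
| 0% | 162 + 82 | 87.2% |
| 10% | 145.8 + 73.8, about 146 + 74 | 83.6% |
| 20% | 129.6 + 65.6, about 130 + 66 | 79.0% |

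The 10% row uses the whole numbers and the 20% row the unrounded ones; rounding moves power by no more than about 0.2 percentage points.

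**Step 5. Compare the arm sizes.** Synopsis and Section 10.7: 162 + 82 = 244, a ratio of 1.98 to 1. Section 5: 164 + 82 = 246, a ratio of exactly 2 to 1. The difference is two patients in one arm.

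**The case against.** The strongest reply is that the error does no harm. If 10% is the true loss, the trial has more power than planned; even at 20%, power falls only to 79.0%. That stands, and it keeps the point well short of a fatal flaw.

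Second, the calculation does not mirror the planned analysis. The full analysis set keeps every randomized patient, missing Month 6 values are multiply imputed, patients who stop early are also to be assessed at the original six-month time point, and the ANCOVA adjusts for baseline GFR. The power figures above are therefore completer t-test approximations on the protocol's own planning basis, not the power of the primary analysis. That also stands, but it does not make 10% lead to 244.

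Third, the 240-260 range covers 244, 246 and 254 but not 226. This suggests that about 244 was the intended size and that the stated rate or the formula is the slip. It is a fair inference about intent, but an approximate range does not say which arm size or drop-out rate applies.

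Finally, 162 against 164 is editorial in size. Agreed, but both figures are current text and only one can be the target.

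**Conclusion.** The point holds. The evaluable sample size is right and the drop-out step is wrong as written. At 10% the requirement is 150 + 76 = 226; the stated 244 is 18 patients (8%) higher and allows for about 17% loss. Section 5 separately disagrees with the synopsis and Section 10.7 by two patients in the Certican arm.

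The consequence is modest: power by the protocol's t-test stays between about 79% and 84% for losses of 20% down to 10%. This rests on the stated difference of 8 ml/min and SD of 19 ml/min, and on counting only completers. The documents do not show which figure is the mistake, so the 20% reading is a possibility and not a finding. It should be corrected because the number sets the recruitment target and the protocol alone fixes it.

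**What to change.** State the intended drop-out rate and the inflation formula n / (1 − d), then make the figures agree. Two repairs need no extra patients:

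- Keep 162 + 82 = 244 and restate the allowance as about 17%. A loss of one in six (16.7%) gives these arm sizes exactly: 135/(5/6) = 162 and 68/(5/6) = 81.6, rounded up to 82. This also fits the 240-260 range. The sponsor should confirm that it is a loss it actually expects, since the protocol offers no support for 17% beyond the arithmetic.
- Keep 10% and restate the target as 150 + 76 = 226. The 240-260 range would then need changing too.

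In either case, give the same arm sizes in the synopsis (Population and Sample size), Section 5 and Section 10.7, replacing 164 in Section 5 unless it is the intended figure. The cost is wording in those places. Only if the sponsor confirms that 20% was meant would the target rise, to 169 + 85 = 254, ten more than now and still within the stated range.

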## **11 Discussion and rationale for study design features**

The study design includes an initial phase of 6 weeks with an Sandimmun® Optoral based immunosuppressive regimen which is required by clinical needs. Dose adjustments after randomization to the treatment regimens in the CNI-free group follows experience from previous clinical trials with everolimus (see [Section 1](#) of this protocol).

Blinding of the two study treatments was not reasonable in this trial because dosing of Sandimmun® Optoral and Certican® has to be based upon trough levels. Therefore the study has to be planned open-label. However, the endpoint of the study is GFR which is an objective outcome variable depending on laboratory measures. An influence of open-label treatment on this primary outcome variable is limited because dosing behavior will mainly be governed by drug trough levels but only in a few expected cases of overt renal toxicity by the creatinine level.

Because early cyclosporine withdrawal in previous studies was associated with better renal function, but slightly increased frequency of rejection, cyclosporine withdrawal in this study is attempted with the additional application of 2 doses of Basiliximab. It is to be expected that the immunological risk at this point in time is low, and the benefit of cyclosporine elimination will continue. For this purpose, a CNI-free regimen will be compared with a standard Sandimmun® Optoral based immunosuppressive regimen. It is expected, that the CNI-free regimen will result in a

superior renal function and that the CNI-free are as safe and effective as the standard Sandimmun® Optoral-based regimen with regard to occurrence of biopsy proven acute rejection episodes, graft loss, death, and lost to follow up, as well of treatment failure (composite endpoint).

A maintenance treatment period of 18 weeks under both regimens is considered sufficiently long to explore any meaningful differences between the groups in the glomerular filtration rate, which is the primary efficacy outcome measure. This has been confirmed in previous clinical trials, where CNI-withdrawal led to an immediate and significant improvement of renal function within a few weeks. The design chosen for this study was also used in other switch studies ([Johnson et al., 2001](#); [Flechner et al., 2002](#)).

In summary, the present study design is adequate for investigating the influence of different immunosuppressive regimens with standard or without CNI on short- and long-term renal function.

## **Appendix 1: Administrative procedures**

### **Regulatory and ethical compliance**

This clinical study was designed and shall be implemented and reported in accordance with the ICH Harmonized Tripartite Guidelines for Good Clinical Practice, with applicable local regulations (including European Directive 2001/83/EC and US Code of Federal Regulations Title 21), and with the ethical principles laid down in the Declaration of Helsinki.

### **Responsibilities of the investigator and IRB/IEC/REB**

The protocol and the proposed informed consent form must be reviewed and approved by a properly constituted Institutional Review Board/Independent Ethics Committee/Research Ethics Board (IRB/IEC/REB) before study start. A signed and dated statement that the protocol and informed consent have been approved by the IRB/IEC/REB must be given to Novartis before study initiation. Prior to study start, the investigator is required to sign a protocol signature page confirming his/her agreement to conduct the study in accordance with these documents and all of the instructions and procedures found in this protocol and to give access to all relevant data and records to Novartis monitors, auditors, Novartis Clinical Quality Assurance representatives, designated agents of Novartis, and regulatory authorities as required.

### **Informed consent**

Eligible patients may only be included in the study after providing written (witnessed, where required by law or regulation), IRB/IEC/REB-approved informed consent, or, if incapable of doing so, after such consent has been provided by a legally acceptable representative of the patient. Informed consent must be obtained before conducting any study-specific procedures (i.e., all of the procedures described in the protocol). The process of obtaining informed consent should be documented in the patient source documents.

The informed consent form that complies with regulatory requirements and is considered appropriate for this study is provided separately. Any changes to the consent form suggested by the investigator must be agreed to by Novartis before submission to the IRB/IEC/REB, and a copy of the approved version must be provided to the Novartis monitor after IRB/IEC/REB approval.

### **Amendments to the protocol**

Any change or addition to the protocol can only be made in a written protocol amendment that must be approved by Novartis, Health Authorities where required, and the IRB/IEC/REB. Only amendments that are required for patient safety may be implemented prior to IRB/IEC/REB approval. Notwithstanding the need for approval of formal protocol amendments, the investigator is expected to take any immediate action required for the safety of any patient included in this study, even if this action

represents a deviation from the protocol. In such cases, Novartis should be notified of this action and the IRB/IEC/REB at the study site should be informed within 10 working days.

### **Discontinuation of the study**

Novartis reserves the right to discontinue this study under the conditions specified in the clinical trial agreement.

### **Study drug supply and resupply, storage, and tracking**

Study drugs must be received by a designated person at the study site, handled and stored safely and properly, and kept in a secured location to which only the investigator and designated assistants have access. Upon receipt, the study medication should be stored according to the instructions specified on the drug labels. Clinical supplies are to be dispensed only in accordance with the protocol.

Medication labels will be in the German and comply with the legal requirements. They will include storage conditions for the drug and the randomization number but no information about the patient.

The investigator must maintain an accurate record of the shipment and dispensing of study drug in a drug accountability ledger. Drug accountability will be noted by the field monitor during site visits and at the completion of the trial. Patients will be asked to return all unused study drug and packaging at the end of the study or at the time of study drug discontinuation.

At the conclusion of the study, and, as appropriate during the course of the study, the investigator will return all used and unused study drug, packaging, drug labels, and a copy of the completed drug accountability ledger to the Novartis monitor or to the Novartis address provided in the investigator folder at each site.

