2. Reminder (Visit 2/Week 2):  
By a reminder that will be included in the CRF of the Week 2 assessments, site will be reminded to schedule the next Visit 3 (Week 7) on time
3. Randomization (BL 2):  
At day of randomization, the site will provide the patient information of eligible patients to the designated CRO by fax.  
Depending on the stratum (previous rejections yes/no), the designated CRO randomization department will allocate the patient the next free consecutive randomization number allocated to the site per stratum. Randomization number and allocated treatment (according to the randomization list) will be provided to the site by fax.

The randomization number will be entered on the CRF of an individual patient.

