## **6.5 Treating the patient**

### **6.5.1 Study drug administration**

Each study site will be supplied by Novartis with study drug (everolimus, Certican®) for patients who are treated in the Certican®-group. Study drug will be provided as tablets, packaged in boxes containing strips of blisters packed tablets, and labeled as RAD001 Tablets. Study drug will be available in 0.75 mg strength. Additional medication for dose titrations will be provided in 0.5 mg and 1.0 mg strength.

One component of the box consists of a 2-part label which includes an identifier of each single box of study medication. Before dispensing the study medication to an

individual patient, investigator staff must enter the 4-digit patient code and the date of dispensing of the medication box on both parts of the label. The outer part of the label will be detached from the packaging and affixed to the source document (Drug Label Form in the CRF) containing that patient's unique patient number.

For the other immunosuppressive drugs (Simulect® induction therapy, Sandimmun® Optoral, Myfortic®, Corticosteroids) the patient will receive a prescription.

Patients randomized to Certican®-group will receive additional doses of Simulect® (each 20 mg) on Week 7 and 12 as rejection prophylaxis. These doses will be provided as investigational drug.

The prescribed total daily dosage of the immunosuppressive drugs should be divided in two (equal) doses, applied 12 hours apart (i.e. 08:00 a.m. and 08:00 p.m.).

The investigator should instruct the patient to take the study drug exactly as prescribed in order to promote compliance. All dosages prescribed and dispensed to the patient and all dose changes during the study must be recorded on the Dosage Administration Record CRF.

In patients randomized to the Certican® regimen, withdrawal of Sandimmun® Optoral and commencement of Certican® will be performed in different steps as described below, starting at Visit 3 (Week 7).

- Step 1: Day 1 morning: Myfortic® + Sandimmun® Optoral  
Day 1 evening: Myfortic® + Sandimmun® Optoral + Certican® (3 mg)
- Step 2: Day 2 morning: Myfortic® + Certican® (1.5 mg)  
Day 2 evening: Myfortic® + Certican® (1.5 mg)
- Step 3: Day 3 morning: Myfortic® + Certican® (TL 5 – 10 ng/mL)

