### **Visit 3 (Week 7 post Tx) – Baseline visit 2**

This visit may be performed within a time window of week 7 and week 8.

1. Patient's eligibility for the study according to in- and exclusion criteria will be checked
2. The patient will be randomized to one of the two treatment arms taking stratification into account (occurrence of rejection between BL1 and BL2).  
Study medication for the following treatment weeks will be handed over to the patient; amount and mode of administration will be explained to the patient
3. A complete physical examination will be performed.
4. (Changes in) smoking status will be recorded and the cardiovascular risk (Framingham Score, see [Appendix 7](#)) will be calculated.
5. Vital signs will be measured.

6. Venous blood will be drawn for measurement of hematology and biochemistry (complete program)
7. An oral glucose tolerance test (OGTT) with a concomitant insulin measurement will be performed.
8. Venous blood will be drawn for measurement of viral serology
9. Venous blood will be drawn for measurement of the C0-h level of cyclosporine
10. Urinalysis will be performed, the Glomerular Filtration Rate (GFR) will be assessed.
11. Changes in Concomitant medications / significant non-drug therapies will be recorded
12. (Changes in) immunosuppressive medication will be recorded
13. Information on rejection episodes, renal biopsies, hospitalization, infections, and other (S)AEs that occurred since the last visit will be recorded.
14. Optionally – if part of center standard procedure – a control biopsy may be taken. Control biopsies should be assessed by a central nephropathologist and should only prompt therapy in cases of severe rejection, infection or toxicity. In order to avoid any bias, which could interfere with the objectives of the study, investigators should be kept blinded until completion of the study.

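### The protocol has two conflicting rules for the Certican label; the one that puts the randomization number on it could expose allocations within the number range already shipped to a site

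*Protocol*

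**What the plan says.** Three places describe how Certican is labelled or linked to a patient.

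- Appendix 1, on study drug supply, sets the label content: "They will include storage conditions for the drug and the randomization number but no information about the patient". The same section has sites store the drug, once received, as its labels instruct.
- Section 6.3 says: "Each patient will receive only that treatment regimen which is labeled with the randomization number allocated to him/her".
- Section 6.5.1 describes a two-part label with an identifier for each single box. Before dispensing, "investigator staff must enter the 4-digit patient code" and the dispensing date on both parts. It mentions no randomization number.

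The surrounding rules on supply and allocation are these.

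- Supply (Section 6.5.1): "Each study site will be supplied by Novartis with study drug" for patients in the Certican group. Simulect doses 3 and 4, given only in that group, are also provided as investigational drug. For the other immunosuppressants "the patient will receive a prescription".
- Order of use (Section 6.3): "The randomization numbers are sequentially allocated to the patients per center in the order of inclusion in the randomized treatment period". At randomization the CRO assigns "the next free consecutive randomization number allocated to the site per stratum" and faxes the number and treatment to the site. The two rejection strata use different numbers, and the block length is withheld from centers.
- Timing (Section 7, Visit 3, the randomization visit): "Study medication for the following treatment weeks will be handed over to the patient".

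**The concern.** In an open-label trial, keeping the next assignment unknown until the patient is committed is the main protection against selection bias. The protocol clearly wants that protection, since it allocates centrally by fax and withholds the block length. A label bearing the randomization number, on stock that exists for one arm only, works against both measures.

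There is room for selection at Baseline 2. Several criteria need judgement: whether creatinine is stable, whether an infection would interfere with the study objectives, whether side effects are intractable. The visit may also fall anywhere in Weeks 7 and 8. Section 11 defends the open-label design on the grounds that GFR is an objective laboratory measure and that dosing follows trough levels. That answers concerns about measurement and dosing, but not about who is randomized into which slot.

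**Working it through.** The point concerns consistency between sections, so the protocol has no figure of its own to reproduce.

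**Step 1: do the label rules agree?** Under Appendix 1 and Section 6.3 the label carries the randomization number, and Appendix 1 adds that it carries nothing about the patient. Under Section 6.5.1 it carries a box identifier, and a patient code is added by hand. The identifier cannot simply be the randomization number, because it is specific to a single box while a patient receives medication at Visits 3, 5 and 6. The rules therefore differ, and no text ranks one above the other. Section 6.5.1 also does not say that its identifier is independent of the randomization list.

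**Step 2: is the label on the drug before allocation?** Appendix 1 has sites follow the storage instructions on the labels once drug is received, so a label with storage conditions is present at receipt. The same section lists storage conditions and the randomization number together as label content. Hand-over takes place at the visit at which the patient is randomized, so stock must normally be on site by then. Both facts point to numbered stock before allocation. Neither states it.

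**Step 3: what would numbered stock reveal?** Control drugs are prescribed, so a Control number never has a Certican box. Numbers are used consecutively per site and stratum, and the strata have different numbers. Within the range for which boxes have been shipped, a number with a box is Certican and a gap is Control. Beyond the last box nothing can be inferred, because a missing number may be Control or may not yet have been shipped.

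**Step 4: how much more predictable is that?** The allocation ratio is 2:1 (Section 6.3).

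- No information, always guessing Certican: 2/3 = 67% correct.
- Block length and all earlier allocations known, block of 3 (assumed, since the length is withheld): the first guess is right with probability 2/3; the second with 2/3 × 1/2 + 1/3 × 1 = 2/3; the third always. The average is (2/3 + 2/3 + 1)/3 = 7/9 = 78%.
- The same by simulation for assumed blocks of 6, 9 and 12: 74%, 73% and 72%.
- Numbered stock, within the shipped range: 100%.

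**Step 5: can this be turned into bias in GFR?** A simple expression for the shift in an arm mean is the share of slots steered times the prognostic difference left after covariate adjustment. The protocol gives neither quantity, so no figure in ml/min follows from it.

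**Step 6: patient code.** In Section 6.3 the patient identification has two parts: a four-digit center number and a patient part that starts at 00001 in each site. A four-digit code therefore matches the center part only.

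**The case against.** The strongest reply is that Section 6.5.1 is the operational section and reads as interchangeable stock. Boxes are identified individually and linked to a patient at dispensing, which suits trough-guided dosing with three tablet strengths. Under that scheme the shelf reveals nothing. A randomization number could also be written on after the fax arrives, and the ban on patient information may describe only the printed text. Section 6.3 is weak support too, because the control regimen is prescribed trade ware and cannot literally carry a sponsor label for every patient. This stands in part: it makes the exposure conditional. It does not remove the conflict. If Section 6.5.1 is what is intended, the wording in Appendix 1 and Section 6.3 is wrong and still needs correction.

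The second reply is that steering would be hard. About 244 randomizations over 24 months (some 104 weeks) at 8 to 12 centers is 244/104 = 2.35 per week, or 0.20 to 0.29 per site per week. With a window of Weeks 7 and 8, deferral often changes nothing, because no other patient at that site and stratum is randomized in between. Inclusions are reported to the CRO at Baseline 1 and reasons for non-randomization are recorded, so selective exclusion would leave a trail. The primary model adjusts for center, prior rejection and Baseline 2 GFR. All of this stands and limits the likely damage. It does not restore concealment: exclusion on a judgement criterion remains possible, and the covariates remove only the selection that they capture.

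A reader might infer that the shelf stock reveals every upcoming allocation. The documents do not support that. No sentence says that numbers are printed before allocation, Section 6.5.1 describes a scheme that would disclose nothing, and only the shipped range would be exposed in any case.

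**Conclusion.** The point holds as a conflict between label rules, one of which would break allocation concealment if followed. Appendix 1 and Section 6.3 put the randomization number on the label; Section 6.5.1 does not.

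The consequence rests on two conditions: that Appendix 1 and Section 6.3 are the rules followed, and that the number is on the stock at receipt. The storage instruction and the Visit 3 hand-over make the second plausible without establishing it. If both hold, allocations within the shipped range are fully predictable, against 67% by simple guessing and about 72% to 78% for a site that knew the block length (blocks of 12 down to 3, assumed) and all earlier allocations. The effect on the treatment comparison cannot be sized from the protocol, and any figure in ml/min would be invented.

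The mismatch over the four-digit code is clerical. The detached label is affixed to a form bearing the unique patient number, so traceability is not lost, and the mismatch has no bearing on concealment.

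**What to change.** - **Appendix 1:** delete the randomization number from the pre-printed label content, and make clear that the bar on patient information applies to printed text only.
- **Section 6.3:** remove the statement that the regimen is labelled with the randomization number. Say instead that each patient receives the regimen assigned to that number.
- **Section 6.5.1:** keep the box identifier and state that it is unrelated to the randomization list. Have the full patient identification, and the randomization number if wanted, written on the box only after the CRO's fax has arrived. Replace the four-digit patient code with the two-part identification of Section 6.3. Apply the same rule to the Simulect supplied for doses 3 and 4.

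The cost is a change of label text and a written amendment, with the approvals that Appendix 1 requires. No new procedure is needed, because Section 6.5.1 already describes the box-identifier scheme. The change should be made before numbered stock reaches a site, since concealment once lost cannot be restored in the analysis.
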